## SUMMARY

**Rationale:** up to 60% of patients with head and neck cancer are malnourished upon first presentation. Malnutrition has been associated with more adverse events and lower quality of life and survival. According to current Dutch guidelines, patient with high risk of malnutrition receive pretreatment dietary treatment. A recent study has shown that patients with low to medium risk of malnutrition, may benefit from additional screening and subsequent nutritional prehabilitation.

**Objective:** to investigate the effect of nutritional prehabilitation on adverse events in patients with locoregionally advanced head and neck cancer and with low to medium risk of malnutrition. To evaluate its effect on patient-reported quality of life outcome measures, recurrence and (disease-specific and overall) survival. To evaluate the cost-effectiveness of nutritional prehabilitation compared to standard care.

**Study design:** a single-center, non-blinded, randomized controlled trial.

**Study population:** patients with stage III and stage IV primary mucosal squamous cell carcinoma located in the oral cavity, oropharynx, hypopharynx or larynx treated with curative intent and with low or medium risk of malnutrition.

**Intervention:** one group will receive nutritional prehabilitation and one group will receive standard care (which means they will not receive nutritional prehabilitation).

**Main study parameters/endpoints:** adverse events (i.e., intra- and postoperative complications and (chemo)radiotherapy toxicity). Complications will be measured within 30 days after surgery using the Clavien-Dindo classification. Toxicity will be evaluated using the Common Terminology Criteria for Adverse Events, version 4.0, 6 weeks after the start of (chemo)radiotherapy.

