## 8. METHODS

### 8.1 Study parameters/endpoints

#### 8.1.1 Main study parameter/endpoint

The primary outcome will be adverse events (intra- and postoperative complications and (chemo)radiotherapy toxicity). Relevant complications include hemorrhage, infection and wound healing disorders including dehiscence and fistula.

Complications will be measured within 30 days after surgery using the Clavien-Dindo classification and evaluated during hospital stay and planned and unplanned outpatient visits [22]. Clavien-Dindo grade  $\geq 2$  complications will be deemed clinically relevant. Toxicity will be evaluated using the Common Terminology Criteria for Adverse Events (CTCAE), version 4.0, at 6 and 12 weeks after the start of (chemo)radiotherapy [23]. The following domains are scored within the CTCAE: xerostomia, taste, throat pain, oral pain, general pain, dysphagia, hoarseness and mucositis. Clinically relevant toxicity will be defined as CTCAE toxicity grade  $\geq 3$ , irrespective of the mentioned domains.

Both complications and (chemo)radiotherapy toxicity are evaluated as part of our current standard practice.

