## **8.3 Study procedures**

*Procedures that are part of standard clinical practice:*

- Diagnostic head and neck CT scans, which will be used to measure pre-treatment CSMA at the level of C3 [29, 30, 32]. The acquired CSMA at the level of C3 will be converted to CSMA at the level of L3 and subsequently corrected for patients' squared height to obtain the LSMI. Low LSMI will be defined as lower than 46.5 cm^2/m^2 for men and lower than 37.9 cm^2/m^2 for women [13];
- Intra- and postoperative complications measured within 30 days after surgery using the Clavien-Dindo classification;

- (Chemo)radiotherapy toxicity measured 6 and 12 weeks after the start of (chemo)radiotherapy using the CTCAE version 4.0;
- EORTC H&N35 measured for two years at baseline and at 3, 6, 12, 18 and 24 months;
- EORTC C30 measured for two years at baseline and at 3, 6, 12, 18 and 24 months;
- EQ-5D-5L measured at baseline and at 3, 6, 12, 18 and 24 months.

*Procedures that are not part of standard clinical practice and all of which will not postpone diagnostic procedures or treatment:*

- Grip strength, which will be measured using a Jamar hydraulic handheld dynamometer as recommended by the American Society of Hand Therapists and expressed in kilograms. Patients will be asked to squeeze maximally with each hand. Each hand will be measured three times. Low grip strength will be defined as lower than 27 kg in men and lower than 16 kg in women [25]. This measurement will be performed at baseline and takes less than five minutes to complete;
- BIA-measurements to estimate body composition, including body fat and muscle mass, using a weak electric current that flows through the body. The measurement will be performed at baseline, just before the treatment starts, and three months after the final treatment. It takes on average 15 minutes to complete;
- EAT-10 in the first two years of follow-up at baseline and at 3, 6, 12, 18 and 24 months after last treatment. The EAT-10 consists of 10 questions in three domains: functional, emotional and physical. Time to complete the EAT-10 is on average two minutes;
- iMCQ in the first year of follow-up at baseline and at 3, 6 and 12 months after last treatment. The iMCQ consists of 20 questions. Time to complete the iMCQ is on average 10 minutes;

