#### **8.5 Replacement of individual subjects after withdrawal**

To anticipate withdrawal of 5% of subjects, three more subjects than needed will be recruited per group. In case of withdrawal before randomization, the subject will be replaced for a new subject. If more than 5% of subjects withdraw before completing the intervention (i.e., nutritional prehabilitation) or before completing the primary endpoint (intra- and postoperative complications within 30 days after surgery or toxicity six weeks after the start of (chemo)radiotherapy), they will be replaced with additional subjects to ensure a total of 128 subjects for the evaluation of the primary endpoint.

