### **9.2 AEs, SAEs and SUSARs**

#### **9.2.1 Adverse events (AEs)**

Adverse events are defined as any undesirable experience occurring to a subject during the study, whether or not considered related to the experimental intervention (i.e., nutritional prehabilitation). All adverse events reported spontaneously by the subject or observed by the investigator or his staff will be recorded up until 6 weeks after last treatment, thereafter only SAEs will be recorded.

Any event involving adverse drug reactions, illnesses with onset during the study or exacerbations of pre-existing illnesses will be recorded, including but not limited to clinically significant changes in physical examination findings and abnormal objective test findings (e.g., x-ray, ECG). The criteria for determining whether an abnormal objective test finding should be reported as an AE are as follows:

- The test result is associated with clinically significant symptoms, and/or;
- The test result leads to a discontinuation from the clinical trial, significant additional concomitant drug treatment or other therapy and/or;
- The test result leads to any of the outcomes included in the definition of a SAE, and/or;
- The test result is considered to be clinically relevant by the investigator.

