#### **9.2.2 Serious adverse events (SAEs)**

A serious adverse event is any untoward medical occurrence or effect that:

- results in death;
- is life threatening (at the time of the event);
- requires hospitalisation or prolongation of existing inpatients' hospitalisation;
- results in persistent or significant disability or incapacity;

- is a congenital anomaly or birth defect; or
- any other important medical event that did not result in any of the outcomes listed above due to medical or surgical intervention but could have been based upon appropriate judgement by the investigator.

An elective hospital admission will not be considered as a serious adverse event.

The investigator will report all SAEs to the sponsor without undue delay after obtaining knowledge of the events, except for the following SAEs:

- (prolonged) hospitalisation or intervention due to: postoperative hemorrhage, infection and wound healing disorders, which all can be expected with standard of care (i.e., (major) head and/or neck surgery).
- hospitalisation or intervention due to: (chemo)radiotherapy toxicity such as vomiting, throat pain, oral pain, dysphagia, mucositis and blood value imbalances, which all can be expected with standard of care (i.e., 70 Gy (chemo)radiotherapy).

The sponsor will report the SAEs through the web portal *ToetsingOnline* to the accredited METC that approved the protocol, within 7 days of first knowledge for SAEs that result in death or are life threatening followed by a period of maximum of 8 days to complete the initial preliminary report. All other SAEs will be reported within a period of maximum 15 days after the sponsor has first knowledge of the serious adverse events.

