### 10.1 Primary study parameter(s)

The primary outcome will be adverse events (intra- and postoperative complications and (chemo)radiotherapy toxicity). Relevant complications include hemorrhage, infection and wound healing disorders including dehiscence and fistula. Complications will be measured within 30 days after surgery using the Clavien-Dindo classification and evaluated during hospital stay and planned and unplanned outpatient visits [22]. Clavien-Dindo grade  $\geq 2$  complications will be deemed clinically relevant. Toxicity will be evaluated using the Common Terminology Criteria for Adverse Events (CTCAE), version

4.0, 6 and 12 weeks after the start of (chemo)radiotherapy. The following domains are scored within the CTCAE: xerostomia, taste, throat pain, oral pain, general pain, dysphagia, hoarseness and mucositis. Clinically relevant toxicity will be defined as CTCAE toxicity grade  $\geq 3$ , irrespective of the mentioned domains.

For analysis of between-group differences in the primary outcome, a logistic regression analysis will be performed. The endpoints complications and toxicity will be dichotomized. In case of unbalance between the intervention and the control group, adjusted logistic regression analyses will be performed. A  $p$ -value  $< 0.05$  will be considered as statistically significant.

Subgroup analyses will be performed using the following variables:

- (intended) type of treatment (surgery versus (chemo)therapy)
- Subsite (larynx versus hypopharynx versus oropharynx versus oral cavity)
- Skeletal muscle mass (LSMI in  $\text{cm}^2/\text{m}^2$ )
- Duration of nutritional prehabilitation intervention
- Number of dietetic consultations
- Dietary intake using 24-hour recall

These variables will be added to the regression analyses

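### The toxicity half of the primary endpoint rests on scheduled CTCAE readings with no look-back or combining rule, whereas complications count over a continuous 30-day window

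*Protocol*

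**What the plan says.** The primary outcome has two parts, each turned into a yes/no.

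- **Surgery (8.1.1, repeated in 10.1).** "Complications will be measured within 30 days after surgery using the Clavien-Dindo classification and evaluated during hospital stay and planned and unplanned outpatient visits". Grade 2 or higher counts. This accumulates over a window and includes unplanned contacts.
- **(Chemo)radiotherapy.** In 8.1.1 the CTCAE is applied "at 6 and 12 weeks after the start of (chemo)radiotherapy"; 8.3 lists the same two times, and 10.1 has version "4.0, 6 and 12 weeks after the start of (chemo)radiotherapy. The following domains are scored within the CTCAE". Eight domains are scored and grade 3 or higher counts.

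Two other places give a single time. The Summary states: "Toxicity will be evaluated using the Common Terminology Criteria for Adverse Events, version 4.0, 6 weeks after the start of (chemo)radiotherapy". Section 8.5, describing when a subject has completed the primary endpoint, refers to "toxicity six weeks after the start of (chemo)radiotherapy".

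Adverse events in general are collected continuously, with the end of recording counted from the final treatment. Section 9.2.1 reads: "All adverse events reported spontaneously by the subject or observed by the investigator or his staff will be recorded up until 6 weeks after last". No sentence links these records to the primary endpoint. A maximum grade is mentioned only in 10.2, for the cost-effectiveness analysis.

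**The concern.** The primary objective in section 2 is the effect on adverse events, that is, whether they occur. The surgical rule matches this. The toxicity rule as written yields the patient's grade on one or two dates. Without a look-back period, a severe episode that has settled by the reading leaves no trace in the endpoint, and the two halves of the composite measure different things: occurrence over a window for surgery, and something close to prevalence on fixed dates for (chemo)radiotherapy.

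The protocol itself expects such episodes. Section 9.2.2 exempts from SAE reporting to the sponsor "hospitalisation or intervention due to: (chemo)radiotherapy toxicity such as vomiting, throat pain, oral pain, dysphagia, mucositis and blood value imbalances", as expected under standard care. Four of these (throat pain, oral pain, dysphagia, mucositis) are among the eight endpoint domains.

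At stake are the absolute difference on which the trial was sized, its power, and consistent scoring. The trial is not blinded and care providers grade the outcome (8.2), so whether an earlier peak counts should not be left to the individual assessor.

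**Working it through.** **1. Applying the text to patients.** If a reading grades the current state only:

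- Grade 3 mucositis in weeks 3–5 with an admission, grade 2 at week 6, grade 1 at week 12: no event.
- Grade 3 dysphagia in weeks 7–10 without admission, grade 2 at weeks 6 and 12: no event.
- Grade 3 oral pain present on the week-6 date only: event.

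If each reading scores the worst grade since the previous one, all three are events. The protocol allows either reading. If 6 weeks is the only assessment, the second patient is missed under both.

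**2. The plan's own figure.** Inputs from 4.4: 15% versus 40%, two-sided alpha 0.05, power 80%, 61 per arm. The pooled z formula needs 49 per arm, the continuity-corrected version 57, and Fisher's exact test 56. I do not reproduce 61 exactly, but it errs on the safe side. Power at n = 61 is

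Φ{[Δ − 1.96·√(2p̄(1−p̄)/n)] / √[(p₁(1−p₁)+p₂(1−p₂))/n]}.

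With p̄ = 0.275 and Δ = 0.25: (0.25 − 0.1585)/0.0776 = 1.18, so power is 88% (Fisher 84%).

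**3. Effect of missed toxicity.** Let f be the share of events that are toxicity and m the share of those missed, equal in both arms. The observed rate is the true rate × (1 − f·m). The documents give neither f nor m. With f = 0.5:

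| m | observed rates | difference (points) | z power | Fisher power |
|---|---|---|---|---|
| 0 | 15% vs 40% | 25 | 88% | 84% |
| 20% | 13.5% vs 36% | 22.5 | 83% | 78% |
| 40% | 12% vs 32% | 20 | 77% | 70% |
| 60% | 10.5% vs 28% | 17.5 | 69% | 62% |

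Over a wider range of f, Fisher power passes below 80% at about 10% missed if toxicity is 80–100% of events (79.3% and 78.0%), and at about 20% missed if it is 40–60% (79.3% and 76.5%).

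**4. What m might be.** This is an assumption throughout. An episode with onset t and duration D weeks is seen if it covers week 6 (t between 6 − D and 6) or week 12 (t between 12 − D and 12). With onset uniform over weeks 3–8:

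- D = 2: seen for onset 4–6, 2 of 5 weeks, so 60% missed.
- D = 3 or 4: seen for onset 3–6, so 40% missed.
- D = 5: seen for onset 3–6 and 7–8, so 20% missed.
- D = 6: none missed.

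The onset window matters. For D = 4 the missed share is 20% (onset 2–7), 25% (3–7), 40% (3–8) or 50% (4–8). At f = 0.5 the z power is then about 83%, 82%, 77% and 73%.

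**The case against.** The strongest reply is that silence is not a rule. The protocol says when toxicity is assessed, not that only that day's state is graded. Section 10.2 speaks of complications at 30 days, although 8.1.1 counts them throughout the 30 days, so a time point in this protocol can stand for a cumulative count. A look-back instruction might also sit in the case report form or the SAP, which is not shown. This stands to the extent that a reader might infer that between-visit toxicity definitely scores as no event; the text does not establish that. It does not remove the gap: the protocol fixes the endpoint and its timing, gives two different sets of times, and an SAP cannot restore grades that were never collected.

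A reader might also infer that the trial is underpowered. The documents do not support that either:

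- Several plausible timings keep z power above 80%.
- The miss shares above treat one episode per patient. Eight domains are scored, so a patient is missed only if all are below grade 3 at every reading, and the true patient-level share is probably lower.
- The 15% and 40% come from cited studies; if those rates rest on scheduled readings, the sample size already matches the endpoint.
- Equal misses in both arms leave the rate ratio at 0.375 (15/40 = 12/32). The odds ratio moves only from (0.15/0.85)/(0.40/0.60) = 0.26 to (0.12/0.88)/(0.32/0.68) = 0.29.

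Finally, looking back has a price: 9.2.1 requires no CTCAE grade, so earlier grades must come partly from recall and notes, judged by unblinded staff. That stands and shapes the fix.

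**Conclusion.** The point holds as a gap in the endpoint definition. The toxicity component is tied to scheduled readings, with no look-back period and no combining rule, and the assessment times conflict between the Summary and 8.5 on one side and 8.1.1, 8.3 and 10.1 on the other. Followed literally, the plan can score a severe but resolved episode as no adverse event, against its own objective.

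The likely consequence is dilution of the absolute difference and some loss of power. The range is 88% down to 69% for 0–60% of toxicity missed, on three assumptions: half of events are toxicity, 15% and 40% are cumulative rates, and misses are equal in the two arms. Since the documents give neither episode timing nor the split between surgery and (chemo)radiotherapy, no single value can be defended. The definition should be corrected; the sample size need not be changed on this ground.

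**What to change.** 1. Reconcile the assessment times across the Summary, 8.1.1, 8.3, 8.5 and 10.1.
2. Define the toxicity event as worst CTCAE grade ≥3 in any of the eight domains, from the start of (chemo)radiotherapy to the last scheduled reading. This also settles how readings combine.
3. At each existing assessment, score each domain for the worst grade since start of treatment or since the previous assessment. Check it against the adverse event and hospital records, under one source-check rule applied identically in both arms.
4. Report the same-day grades at the scheduled readings as a supportive analysis.
5. Use the same worst grade in the cost-effectiveness analysis.

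The cost is a wording change and one instruction on the existing CTCAE form, with no extra visit, plus staff time for the record check. The real downside is that grades between visits are less standardised and are assigned by unblinded care providers. The common source-check rule limits this, and the supportive same-day analysis shows how much it matters.

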### **4.4 Sample size calculation**

We performed a power analysis to calculate the sample size needed. Intervention studies evaluating the effect of nutritional prehabilitation in patients with head and neck cancer have not been performed previously. Therefore, the numbers used for the power analysis are based on studies on the association between malnutrition/radiological sarcopenia and adverse events in patients with head and neck cancer. We expect the rate of adverse events in the intervention arm to be 15% based on the rates of adverse events in well-nourished/non-sarcopenic study populations [8, 13]. We expect the rate of adverse events

in the control arm to be 40% based on reported rates of adverse events in malnourished patients [8] and reported odds ratios in studies on the association between sarcopenia and adverse events [13, 14]. To detect a clinically relevant difference of 25% between the intervention and control arm, with a two-sided alpha of 0.05 and a power of 80%, a minimum of 61 patients per arm are needed. With an expected drop-out of 5%, we will include a total of 128 patients. This analysis was performed using G\*Power version 3.1.

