## **8.2 Randomisation, blinding and treatment allocation**

The website randomization tool provided by REDCap will be used. A block randomization will be used with an allocation ratio of 1:1. The randomization chart, including block size, will be established by an independent data manager before the start of the study. Consequently, treatment allocation sequence will be concealed for patients, care providers and researchers (including outcome assessors). The outcome assessors in this study are patients (self-assessment using questionnaires) and care providers (Clavien Dindo classification, CTCAE, recurrence and survival).

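### Adjustment of the primary logistic regression depends on an undefined observed imbalance, and the protocol does not say whether the unadjusted or the adjusted result decides the trial

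*Protocol*

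**What the plan says.** Section 10.1 sets the primary analysis: "For analysis of between-group differences in the primary outcome, a logistic regression analysis will be performed". After dichotomising the endpoints it continues: "In case of unbalance between the intervention and the control group, adjusted logistic regression analyses will be performed". The next sentence says that a p-value below 0.05 "will be considered as statistically significant", without saying which of the two models that p-value comes from. No covariate, measure of imbalance or threshold is attached to the rule.

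The design supplies no default covariate set. Section 8.2 says only "A block randomization will be used with an allocation ratio of 1:1", with no stratification factor.

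Section 10.1 then lists variables for subgroup analyses (treatment type, subsite, muscle mass, duration of prehabilitation, number of consultations, dietary intake) and says that they go into the regressions. That sentence closes the subgroup list. Duration and number of consultations arise after randomisation, so the list cannot serve as a baseline-adjusted primary model.

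Section 3 describes the trial as non-blinded. Section 12.6 has the project leader and research team perform the analyses.

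**The concern.** Two things are fixed badly.

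First, the trigger. With sound randomisation every baseline difference is chance, and a test or threshold on it says nothing about whether a covariate is worth adjusting for. What matters is how strongly the covariate predicts the outcome, and that can be judged beforehand. The protocol names candidates itself: section 8.1.3 reports low skeletal muscle mass as associated with both complications and toxicity, section 1 reports more postoperative complications at medium malnutrition risk, and intended treatment type is recorded at baseline.

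Second, the deciding result. Once the trigger fires, an unadjusted and an adjusted p-value both exist. Because imbalance is undefined, whether it fired is itself a judgement made with the data in hand. At stake are a modest amount of power and the credibility of a single confirmatory p-value.

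**Working it through.** **Inputs from the protocol (section 4.4).** Event rates 15% (intervention) and 40% (control), two-sided alpha 0.05, power 80%, and "a minimum of 61 patients per arm are needed".

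**The plan's own figure.** The usual formulas do not return 61. The pooled z test gives 49 per arm, the continuity-corrected version 57, and Fisher's exact test 56 (80.8% power). At 61 per arm, power is 88.1% (z test) or 84.3% (Fisher), so 61 is conservative. That is a separate matter. What counts here is that an unadjusted analysis at the design rates already exceeds 80%.

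**How often would the rule fire?** It depends on the missing definition.
- Difference of 10 points or more in a 50/50 binary factor, 61 per arm. This means a count difference of at least 7, since 0.10 × 61 = 6.1. The SD of the count difference is √(2 × 61 × 0.25) = 5.52. With continuity correction, 6.5/5.52 = 1.18, a two-sided probability of about 0.24. For at least one of five independent factors: 1 − (1 − 0.24)^5 = 0.75.
- Baseline test at p < 0.10. With four covariates, 1 − 0.9^4 = 0.34; with two, 1 − 0.9^2 = 0.19. Simulation gave 34 to 35% and 19 to 20%.

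So two ordinary readings of the same sentence fire in anything from about a fifth to three quarters of trials, always on chance differences.

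**Simulation A: 61 per arm, 4000 trials per scenario.** Five 50/50 binary factors. Modality is assumed to carry control event rates of 20% and 60% (mean 40%). The rule adjusts for any factor that differs by 10 points or more. The modality contrast is an assumption; the documents give none.

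| Analysis | Rejection under the null | Power at 15% vs 40% |
|---|---|---|
| Unadjusted | about 5% | about 88% |
| Imbalance rule, applied mechanically | about 4% | 88 to 89% |
| Fixed adjustment for modality | about 4.7% | about 92% |
| Unadjusted or rule, whichever is significant | about 5.8% | – |

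**Simulation B: continuous covariates, trigger at baseline p < 0.10.** Power unadjusted / rule / fixed:
- four covariates, odds ratio 1.5 per SD: 88.2 / 88.8 / 90.7%
- four covariates, odds ratio 2.0 per SD: 89.1 / 89.5 / 93.8%
- two covariates, odds ratio 2.5 per SD: 88.8 / 90.1 / 94.1%
- four non-prognostic covariates: 89.2 / 88.8 / 88.6%

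Under the null, the rule rejects at 3.8 to 5.1% and the fixed model at 4.8 to 5.2%. Taking the smallest p-value among the three models rejects at 6.0 to 7.8%. Monte Carlo standard error is about 0.5 point for power and 0.35 point for type I error.

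**Why power rises although the standard error does not fall.** The crude odds ratio is (0.15/0.85)/(0.40/0.60) = 0.265, log −1.33. Its standard error is √[1/(61 × 0.15 × 0.85) + 1/(61 × 0.40 × 0.60)] = 0.444; simulation gives 0.445. Within modality, the odds ratio c that yields 15% overall solves ½[0.25c/(1 + 0.25c) + 1.5c/(1 + 1.5c)] = 0.15. Hence c = 0.22, log −1.51, with a simulated standard error of about 0.49. The ratio of estimate to standard error moves from 1.33/0.445 = 2.99 to 1.51/0.49 = 3.08.

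**Room for covariates.** Expected events: 61 × (0.40 + 0.15) = 33.6, enough for a few terms.

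**The case against.** The strongest reply is that the protocol names logistic regression as the analysis and adjustment as conditional, and that the covariate list, the definition of imbalance and the labelling of sensitivity analyses belong in a statistical analysis plan, which is not shown. The second part stands: an absent covariate list alone would be no finding. But the conditional trigger is written into the protocol, and a later plan could only refine a rule that rests on the wrong criterion.

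Several stronger readings are tempting, and the documents do not support them:

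- *The rule inflates type I error.* Followed mechanically it is slightly conservative. The 5.8% needs someone to count whichever result is significant. The text leaves room for that but does not license it.
- *Precision is lost without adjustment.* On the log odds scale the standard error rises with adjustment (0.445 to about 0.49). The gain is in power, or in the precision of a standardised risk difference.
- *The unadjusted odds ratio is biased towards 1.* It is a valid marginal effect under randomisation. The conditional odds ratio is a different quantity, because odds ratios are non-collapsible.
- *The trial falls below 80% power without adjustment.* At the protocol's own rates it does not.
- *Modality decides which endpoint a patient can have.* A surgical patient given adjuvant (chemo)radiotherapy could have both. Nor do the documents say that modality is settled at randomisation; section 8.1.3 lists only the intended type as a baseline item.

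The choice among sensible covariates (treatment type, malnutrition category, muscle index, subsite) is a matter of judgement. That a choice should be made in advance is not.

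**Conclusion.** The point holds in limited form. The primary model depends on an undefined, chance-driven condition, and the protocol does not say which result is tested at 0.05. The certain harm is ambiguity in the confirmatory analysis of an open-label trial analysed by its own team. The measurable cost is about 2 to 4 points of power against a fixed model, provided the covariates are prognostic to the degree assumed. It is nil if they are not, and the documents do not quantify prognostic strength. Type I error stays at about 4% if the rule is followed strictly, and reaches about 5.8% if either result may count (6.0 to 7.8% with a wider choice of models). This is a worthwhile and cheap correction, not a threat to the validity of the trial.

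**What to change.** Replace the conditional sentence in section 10.1 with one stated primary model: logistic regression of the composite on arm and a small fixed set of baseline covariates, fitted whatever the observed balance. Intended treatment type is the natural first choice, with, for example, malnutrition risk category or lumbar skeletal muscle index. State that the arm effect from this model is the one tested at the two-sided 0.05 level. From the same model, report the standardised risk difference with its 95% confidence interval beside the odds ratio; this is the scale of the 25-point target. Present the unadjusted result as a sensitivity analysis. Keep duration of prehabilitation and number of consultations out of the primary model, because both follow randomisation.

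The cost is a few sentences. The covariates are already collected and the sample size does not change. The drawback is that the conditional odds ratio is a different estimand from the crude one and has a larger standard error on the log scale, which is why the standardised risk difference should accompany it. The amendment should be made before outcome data by arm are examined.
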